## Methods

### Study design

This study is a before-after trial (with each site serving as its own control) in smokers who are hospitalized on the medical wards of four VA hospitals (Figure 1). After a six-month baseline period of enrollment, the research team will conduct focus groups of clinical staff at each site, adapt the strategy for guideline implementation, and train clinical staff at each site. A new cohort of study patients will be enrolled over the subsequent six-month intervention period. Staggering the timing of intervention across sites will allow us to collect concurrent control data for three of the four study sites during intervention; this will enable detection of system-wide trends in the delivery of cessation counseling, measurement reactivity, and other potential confounding factors within each period (except the final period)[24,25]. We considered cluster randomization by hospital, but the cost of conducting such a trial was not feasible due to budgetary constraints (as at least four sites per comparison group are typically required) [26].

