### Organizational change

In the two months between the baseline and intervention periods, we will conduct a focus group that includes one or two of each of the following staff at each site: staff nurse, nurse manager, resident, attending physician, pharmacy director, and smoking cessation counselor (six to nine members in total). The focus groups will ask participants to: describe local smoking cessation practices and the 'smoking culture,' identify barriers and facilitators to changing smoking cessation practices, and suggest strategies that will facilitate change at the facility. Focus groups will also allow the study team to examine work place culture, to understand group norms, and to elicit local perspectives that may deviate from (or challenge) conventional beliefs [61,62]. Summaries of the focus groups will be provided to peer leaders (see below) and will be used to adapt the strategy for guideline implementation to the local context [63-65].

With input from the director of nursing and nurse managers at each site, we will identify a peer leader on each medical ward with the attributes of a change champion [59] and the ability to model counseling skills (five A's), troubleshoot issues during implementation, and assist in presenting group feedback to nursing staff [40]. Peer leaders will receive additional training in smoking cessation counseling and in monitoring the practices of other staff nurses by direct observation and medical record audit (using spot checks). By influencing colleagues through small group discussions, informal consultations, and feedback, the peer leader can facilitate adherence to guidelines [66]. A nurse investigator on the study team will contact each peer leader monthly during the intervention to provide ongoing support and to identify and resolve barriers to change. Notes on these conversations will also be documented in the study log for each site. In one primary care trial, the presence of a clinic champion was strongly associated with referral of smokers to a quit line (OR = 3.4, 95% CI = 2.4-5.0)[67], and local champions have emerged as key determinants of organizational innovation [59,68,69].

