### Statistical analysis

The primary clinical endpoint of this analysis is seven-day PPA at three and six months. The primary process of care endpoints are referral of patients to telephone counseling (or other outpatient cessation counseling) and prescription of recommended pharmacotherapy for smoking cessation. To evaluate the relationship between the intervention and these outcomes, we will use hierarchical logistic regression to adjust for differences in potentially confounding patient and nurse characteristics between the baseline and intervention period cohorts. In these analyses, each patient will be nested within his/her admitting nurse, who will have primary responsibility for providing brief cessation counseling. To compare how the two arms differ in time to first relapse after hospital discharge, we will use Cox proportional-hazards survival analysis methods with time to relapse as the outcome [83]; in this analysis, intra-nurse correlation will be accounted for by using the robust sandwich estimator [84].

To evaluate the hypothesis that staff nurses will have improved decisional balance scores and higher ratings of self-efficacy in providing cessation counseling as a result of the intervention, we will compare values of these measures obtained at the end of the intervention period to pre-intervention values using a repeated measures ANOVA with site included as a covariate (or a site-stratified Wilcoxon signed-rank test, if the data are skewed or heavy-tailed). To determine whether the intervention effect (if any) is modified by nurses' perceptions of their work, we will check the interaction between treatment and nurse ratings of professional status and adequacy of staffing.

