## Discussion

Although it is generally accepted that RCTs provide the highest level of evidence in health care research, randomization in the current study is neither feasible nor acceptable to study participants [24]. Moreover, RCTs are not always the best study design for evaluation of the implementation of complex interventions, which typically include multiple components, target multiple outcomes, or aim to achieve outcomes that are difficult to influence [91]. Using a quasi-experimental design, this study will fill an important gap in the evidence base for smoking cessation in hospitalized patients, as the effectiveness of brief bedside counseling combined with sustained relapse prevention is unclear. The two studies that combined brief inpatient counseling with sustained relapse prevention were limited by insufficient power [92], lack of data on the extent to which the relapse prevention component was implemented [92], and failure to include pharmacotherapy as part of intervention [93].

Limitations of the proposed study design deserve comment. Pre-post changes in outcome may be attributable to 'history' (the influence of events during the study that affect the study outcomes) or 'maturation' (the change of staff performance during the study related to the evolution of clinical skills) [25]. Potential Hawthorne effects should be minimized by employing a sufficiently long intervention period (six months). We will check for any time-related changes in cessation counseling or patients' intention to quit during the enrollment period in each hospital. This will allow us to closely monitor any secular trends (*e.g*., release of new smoking cessation aids, changes in hospital policies) that might impact upon delivery of cessation counseling or cessation outcomes. In addition, we will account for any confounder variables that show significant imbalances between baseline and intervention periods in multivariable analyses.

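### The start is staggered to reveal secular trends, but no stated analysis of the intervention effect uses calendar time, so any drift in quit rates would enter the estimate in full

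*Protocol article*

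**What the plan says.** Study design describes the trial plainly: "This study is a before-after trial (with each site serving as its own control) in smokers who are hospitalized on the medical wards of four" sites. It then gives the reason for the staggered start: "Staggering the timing of intervention across sites will allow us to collect concurrent control data for three of the four study sites during intervention". The stated benefit is that "this will enable detection of system-wide trends in the delivery of cessation counseling, measurement reactivity, and other potential confounding factors within each period", with an exception for the final period, when no hospital is still in its baseline phase.

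For the effect itself, Statistical analysis says that "we will use hierarchical logistic regression to adjust for differences in potentially confounding patient and nurse characteristics between the baseline and intervention period cohorts". Patients are nested within their admitting nurse, and the Abstract adds clustering within hospitals. Patients are analyzed by the period in which they enrolled.

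The Discussion names history and maturation as limitations of a pre-post comparison and then turns to Hawthorne effects. Its response is: "We will check for any time-related changes in cessation counseling" and in patients' intention to quit, hospital by hospital. It says this will allow monitoring of secular trends that could affect counseling delivery or cessation outcomes, and that confounders with significant imbalance between periods will be adjusted for.

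**The concern.** At each hospital every intervention patient enrolls later than every baseline patient, so calendar time and intervention are confounded within a site. Patient and nurse covariates do not remove a change in the background quit rate. The staggered start is the one design feature that could help separate the two, because some hospitals are still in baseline while others have crossed over. The analysis as stated does not use that overlap when it estimates the effect.

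The trend check does not close the gap. It names two upstream measures but no analysis of abstinence, which is the primary clinical endpoint. It is done within each hospital rather than across concurrent hospitals. What it finds has no stated route into the estimate beyond adjustment for measured confounders. A positive result could therefore not be told apart from secular change, although data bearing on that question will have been collected.

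**Working it through.** **Inputs from the protocol article.** 500 baseline and 500 intervention patients, a 12% baseline quit rate, a 7-point target (12% versus 19%), 83% power and a nurse ICC of 0.01 (Sample size calculations); 226 nursing staff (Table 1: 42 + 72 + 60 + 52); two-sided 0.05. Timing: a six-month baseline, then "In the two months between the baseline and intervention periods, we will conduct a focus group", then "A new cohort of study patients will be enrolled over the subsequent six-month intervention period".

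**Inputs assumed.** The drift in quit rate (the document gives none); a stagger of 2, 3, 4 or 6 months (Figure 1 is not shown); equal recruitment over months and sites (125 per site and period); a site ICC of 0 to 0.05 for the random-intercept case.

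**1. The plan's own figure.** Two proportions, 12% versus 19%, 500 per period: 86.5% power without clustering. With 1000/226 = 4.4 patients per nurse, the design effect is 1 + 3.4 × 0.01 = 1.034, and power is 85.4%, or 83.2% with a continuity correction. With an assumed 10 patients per nurse (design effect 1.09), it is 83.5%. The stated 83% is reproduced for the before-after contrast.

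**2. Drift in the before-after contrast.** Period midpoints at a site are 6 + 2 = 8 months apart, so bias = 8 × monthly drift. With an SE of about 2.2 points, the two-sided false-positive rate is Φ(bias/SE − 1.96) + Φ(−bias/SE − 1.96).

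| Assumed drift, points/month | Bias, points | Share of 7 points | False-positive rate |
|---|---|---|---|
| 0 | 0 | 0% | 5% |
| 0.1 | 0.8 | 11% | 7% |
| 0.2 | 1.6 | 23% | 11% |
| 0.3 | 2.4 | 34% | 19% |

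With SE 2.29 the last three rates are 6.4%, 10.8% and 18.2%, so the result depends little on the SE chosen.

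**3. Cost of adjusting for time.** These are calculations on the probability scale with a mean rate of 15.5%. With hospital effects only, SE = √(2 × 0.155 × 0.845 / 500) = 2.29 points.

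Now add fixed hospital effects and a linear month term. Within a site, the variance of month is 4² (between periods) + (6² − 1)/12 (within periods) = 16 + 2.917 = 18.917. The variance inflation is 18.917 / 2.917 = 6.49. The SE is 2.29 × √6.49 = 5.83 points, and power for 7 points is Φ(7/5.83 − 1.96) = 22%. This figure is the same at every stagger, because the linear trend is then learned within sites. Time blocks do draw on the overlap between sites.

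| Model for the time-adjusted estimate | SE, points | Power for 7 points |
|---|---|---|
| Fixed hospitals, linear month | 5.8 | 22% |
| Fixed hospitals, 6-month blocks | 4.6-5.6 | 24-34% |
| Fixed hospitals, 3-month blocks | 5.7-6.5 | 19-23% |
| Random hospital intercept, any of these time terms | 2.6-5.6 | 24-75% |

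The ranges run over staggers of 2 to 6 months and, in the last row, site ICC 0 to 0.05. The upper end needs a site ICC of 0 and a 6-month stagger. Applying the nurse design effect of 1.034 lowers each power figure by about one point or less.

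**The case against.** The strongest reply is that the document promises less than the concern supposes. Study design claims that staggering permits trends to be detected; it does not claim that they will be adjusted for. The Discussion discloses the limitation and mentions trends affecting cessation outcomes. Readiness to quit is recorded at enrollment, so a measured shift in motivation could enter the model as an imbalanced confounder. A sensitivity model is also the kind of thing an article may leave to a fuller plan.

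Part of this stands. There is no outright contradiction, and it would be wrong to say that the protocol disregards cessation trends or ranks history as its chief threat. But the article does state its model, adjustment set and trend checks. As stated, none contains calendar time or a trend analysis of abstinence. Adjustment for measured characteristics does not cover calendar time.

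A second reply is that the drift values are invented. That is so: 0.1 to 0.3 points a month is 1.2 to 3.6 points a year on a 12% base, and nothing in the document supports a particular value. The table shows sensitivity, including no drift at all; it does not predict bias.

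A third reply is that the time-adjusted model is too imprecise to help. With fixed hospitals and linear time the 95% interval is about ±11.4 points (1.96 × 5.83). This is why it should not replace the primary contrast. It still shows readers how far the data can separate intervention from time.

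**Conclusion.** The point holds and should be acted on. If quit rates drift, the stated analysis passes the whole drift between period midpoints into the intervention estimate: 0.8 to 2.4 points, or 11-34% of the target, for the drifts assumed here. If there is no drift, there is no bias from this source.

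Three stronger readings are not supported. First, a reader might infer that the 83% power is wrong or is valid only without a trend. It is reproducible for the before-after contrast; drift threatens attribution, and the lower power belongs to a different model. Second, a reader might take a single figure such as 22% as the power after adjustment. It depends on treating hospitals as fixed, whereas the Abstract specifies random effects, and on a stagger that cannot be read here; the range is about 19-75%. Third, a reader might conclude that the order of crossover must be randomized. That would not remove a trend common to all hospitals, since each still moves from baseline to intervention, and with four sites it balances little.

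**What to change.** 1. **Statistical analysis:** keep the before-after contrast as primary. Prespecify, for abstinence and both process endpoints, a second model with hospital effects and calendar time, preferably in 3- or 6-month blocks so that the cross-site overlap is used. Report it beside the primary with its interval.
2. **Discussion (trend check):** add abstinence to the measures examined for time-related change.
3. **Interpretation:** state that attribution to the intervention is qualified if the time-adjusted estimate is materially smaller, and say beforehand what counts as material. Chance alone can separate the two estimates: with fixed hospitals and linear time, and no trend, the SE of their difference is about √(5.83² − 2.29²) = 5.4 points.
4. **Sample size calculations:** say that 83% refers to the before-after contrast and does not carry over to the time-adjusted estimate. Give the power of the latter for the actual stagger.

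The cost is one additional model per endpoint on data already collected, plus wording. The drawbacks are a wide time-adjusted interval and, because the final period has no concurrent controls, a time effect that rests partly on model assumptions.

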**Outcomes:**

The primary endpoint is seven-day point prevalence abstinence at six months following hospital admission and prolonged abstinence after a one-month grace period. To compare abstinence rates during the intervention and baseline periods, we will use random effects logistic regression models, which take the clustered nature of the data within nurses and hospitals into account. We will assess attitudes of staff nurses toward cessation counseling by questionnaire and will identify barriers and facilitators to implementation by using clinician focus groups. To determine the short-term incremental cost per quitter from the perspective of the VA health care system, we will calculate cessation-related costs incurred during the initial hospitalization and six-month follow-up period.

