### Sample size calculations

Based on the volume of admissions at each study hospital, we plan to screen 7,548 potential subjects who are hospitalized on medical wards for greater than 24 hours during the enrollment period at the four sites. Based on chart review, we estimated smoking prevalence at each site (weighted average = 23%, range 17 to 32%), and determined that approximately 80% of identified smokers will be eligible to participate in the proposed trial. Assuming that 84% of eligible patients consent to participate (based on a recent VA smoking cessation study [47]), we would expect 1,000 subjects to enroll in the study (500 baseline, 500 intervention). Pooling the control group data from studies of general medical inpatients, we estimate a 12% quit rate at six-months (seven-day PPA). Thus, a study sample of 1,000 patients will have 83% power to detect a seven percentage-point difference between periods in six-month quit rates. This effect estimate is consistent with that observed in prior hospital intervention trials that employed a sustained relapse prevention component [16,20,21]. Based on chart reviews at two study sites, we estimate that 12 and 13% of inpatients during the baseline period will be referred for cessation counseling and will receive recommended pharmacotherapy, respectively. The projected study sample will have 81 and 83% power to detect a seven percentage-point difference in these process measures, respectively. These power calculations are based on a hierarchical linear model, with nurse treated as a random factor (and patient outcomes are clustered within nurse); intracluster correlation (ICC) was estimated to be 0.05 for assistance in quitting (which includes offering of pharmacotherapy and arranging follow-up), and 0.01 for abstinence, based on data from the AHRQ Smoking Cessation Guideline Evaluation Trial [77].

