We will use an intent-to-treat approach in which patients are analyzed according to the period in which they were enrolled. In our analysis of three- and six-month cessation rates, those who are lost to follow-up will be considered failures (*i.e*., still smoking). Using this approach, however, some bias may be introduced on account of informative censoring (even if the pattern of missingness is evenly distributed across baseline and intervention periods). For this reason, we will also conduct analyses to examine the patterns of missingness, and will perform sensitivity analyses to compare intervention effects under a range of assumptions regarding the mechanism of missingness [85,86]. All tests will be two-sided and will use a p-value of 0.05 for statistical significance. To fit the hierarchical models, we will use SAS (PROC GLIMMIX).

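### The abstract promises clustering by nurse and hospital, the analysis and power sections name only the nurse, and the 83% power makes no allowance for hospital-by-period variation

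*Protocol article*

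**What the plan says.** All references are to the protocol article.

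- Abstract, Outcomes: "we will use random effects logistic regression models, which take the clustered nature of the data within nurses and hospitals into account".
- Methods, Statistical analysis: in the hierarchical logistic models "each patient will be nested within his/her admitting nurse, who will have primary responsibility for providing brief cessation counseling". The Cox model for time to relapse has a sandwich estimator for correlation within nurse. Site is named in this section only for the nurse survey, as a covariate or stratum.
- Methods, Sample size calculations: "a study sample of 1,000 patients will have 83% power to detect a seven percentage-point difference between periods in six-month quit rates". The baseline quit rate is taken as 12%, with 500 patients per period. The model behind the figure is hierarchical, "with nurse treated as a random factor (and patient outcomes are clustered within nurse"; the intracluster correlation is "0.01 for abstinence, based on data from the AHRQ Smoking Cessation Guideline Evaluation Trial".
- Methods, Study design: four hospitals, each compared with itself before and after, with staggered start dates.
- Discussion: events during the study are acknowledged as a limitation, and time trends in counselling and intention to quit are to be checked in each hospital. No hospital or hospital-by-period term is placed in the primary model.

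**The concern.** The article gives two accounts of the model that decides the primary comparison. One has a hospital level and the other does not name one.

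The level matters because exposure does not change nurse by nurse. A whole hospital moves from baseline to intervention, after its own focus group and with locally adapted electronic tools. A change in local policy, or a stronger or weaker intervention effect at one site, shifts all of that hospital's patients in one period together. A nurse intercept that is constant over time does not absorb such a shift. A model without a term for it treats about 125 jointly shifted patients per hospital and period as nearly independent. The interval for the intervention effect would then be too narrow, and the planned power would not be reached.

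**Working it through.** **Inputs.** Quit rates 12% and 19%, 500 patients per period and nurse-level correlation 0.01 (Sample size calculations). Two-sided 5% level (Statistical analysis). Nursing staff 42 + 72 + 60 + 52 = 226 (Table 1). Two assumptions are mine: all listed staff admit study patients, and the hospitals enrol equally, giving 500/4 = 125 patients per hospital and period.

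**Step 1. Reproduce the 83%.** Patients per nurse: m = 1000/226 = 4.42. Design effect: 1 + (4.42 − 1) × 0.01 = 1.034. Effective n per period: 500/1.034 = 483.6.

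Power = Φ{[d − 1.96·√(2p̄q̄/n)] / √[(p₁q₁ + p₂q₂)/n]}, with d = 0.07, p̄ = 0.155, 2p̄q̄ = 0.26195 and p₁q₁ + p₂q₂ = 0.1056 + 0.1539 = 0.2595.

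This is Φ[(0.07 − 0.0456)/0.02317] = Φ(1.05) = 85.4%. Subtracting 1/n from d as a continuity correction gives 83.2%, which matches the stated figure. The 83% therefore follows from nurse-only inputs.

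**Step 2. A constant hospital effect.** With hospital correlation ρ, and correlation r between a hospital's effects in its two periods, the variance of the before-after difference is multiplied by 1 + (125 − 1)ρ − 125ρr. If hospital effects do not change (r = 1), this is 1 − ρ, or 0.99 at ρ = 0.01. Combined with the nurse factor 1.034, power is 85.7% and type I error 4.9%. A hospital intercept therefore leaves the result essentially unchanged.

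**Step 3. Variation between a hospital's two periods.** Let ρ_hp be the correlation within a hospital-period that is not shared across periods. Then DE = 1.034 + 124·ρ_hp. Power uses the Step 1 formula without continuity correction, with n = 500/DE. If the nurse-only standard error is kept, the true type I error is 2[1 − Φ(1.96/√(DE/1.034))]. The corresponding SD of the quit rate is √(ρ_hp × 0.155 × 0.845).

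| ρ_hp (assumed) | SD of quit rate (points) | DE | Power | Type I error |
|---|---|---|---|---|
| 0 | 0 | 1.034 | 85.4% | 5.0% |
| 0.001 | 1.1 | 1.158 | 81.2% | 6.4% |
| 0.002 | 1.6 | 1.282 | 77.2% | 7.8% |
| 0.005 | 2.6 | 1.654 | 66.3% | 12.1% |

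In the Step 2 form, a hospital correlation of 0.01 that is 0.9 stable between periods gives a factor of 1 + 1.24 − 1.125 = 1.115, power 81.4% and type I error 6.3%.

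**Step 4. Cost of making hospital-by-period the error term.** Four before-after differences leave 3 degrees of freedom. A noncentral t calculation gives power of about 54% at ρ_hp = 0 and 38% at 0.005.

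**The case against.** The strongest reply is that the analysis is not shown to be nurse-only. Statistical analysis says patients are nested within nurses, not that this is the only level, and the Abstract says the same kind of model handles hospitals. The article is condensed, and an analysis plan that is not shown might set out the full random-effects structure. This stands in part: the fair description of the analysis is that the article is inconsistent, and only the power calculation is firmly nurse-only. But two stated models that differ are not merely detail left to another document, and the same section does name site for the nurse survey.

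The second reply also stands. A reader might infer that the error bars are too narrow and the 83% too high as a matter of fact. The documents do not support that, because both need hospital-by-period variation and no value for it is given. Nor would adding the hospital intercept that the Abstract suggests cure the problem (Step 2).

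A reader might also carry the plan's 0.01 to the hospital-period level and obtain 53% power and 19% type I error. That 0.01 is a nurse-level correlation, which may already contain whatever is shared across a hospital. Using it here could assign all of it to shifts between periods, so it is not a plan-based estimate.

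Nor do the differences between sites in Table 1 and in smoking prevalence (17 to 32%) show confounding by hospital. They do not show that the mix of hospitals changes between periods, and all four sites enrol for six months in each.

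Finally, the staggered starts and the planned trend checks show that the threat was recognised. They monitor it but do not enter the standard error or the power.

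**Conclusion.** The point holds in a conditional form. The Abstract disagrees with Statistical analysis and Sample size calculations on whether hospital is a level in the patient-outcome models. The 83% is reproduced from nurse-only inputs, so it contains no allowance for hospital-by-period variation. Any positive amount makes nurse-only intervals too narrow and lowers power; the direction is certain and the size unknown.

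Over the assumed range of 0.001 to 0.005, power falls from about 85% to between 81% and 66%, and type I error rises to between 6.4% and 12%. These figures rest on equal hospital sizes, on all 226 staff acting as admitting nurses, and on normal approximations with no small-sample penalty. At zero such variation, nothing is lost.

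**What to change.** 1. Make the Abstract, Sample size calculations and Statistical analysis describe one model.
2. In every patient-level model, include hospital as a four-level fixed effect with nurse as the random effect; in the Cox model, use hospital as a covariate or stratum. Stable differences are then removed even if the enrolment mix shifts between periods.
3. Report hospital-specific effects with a test of heterogeneity.
4. Report a sensitivity interval that allows for hospital-by-period variation. Making that term the primary error term is a debatable trade, given the roughly 54% power at zero variation, so it belongs in a sensitivity analysis.
5. Restate the 83% as assuming no hospital-by-period variation, and give a range such as the one above.

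The cost is wording, three fixed-effect parameters and one extra analysis. The stated power will look less favourable, and the sensitivity interval will be wide because there are only four hospitals. Hospital-specific estimates will also be imprecise: with 125 patients per period, the 95% half-width is about 1.96 × √(0.2595/125) = 8.9 points before any nurse clustering, so a non-significant heterogeneity test should not be read as evidence that the effects are equal.
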